#### Sample size

Based on pilot data and power analysis with beta = .80, alpha = .05, effect size f = .25 and an estimated correlation between pre- and post-measures of .50, a total of 98 patients are required: 49 patients receiving LEAP and 49 controls. With an estimated drop-out rate of 30%, we will enroll 128 participants (64/arm). As there is a minimum of 4 participants in a LEAP group, length of time between initial assessment and first session of LEAP will vary for patients. This variation will need to be considered a covariate.

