##### Self-report and interview data

The project includes three assessment timepoints when participants complete questionnaires: T1, 3-month (T2) and 6-month follow-up (T3). Apart from the medical record data at T1, all measurements are distributed to participants through BASS (see below) after study consent. T1 includes self-reports CET, DERS, DSM-5, and Active-Q; T2 includes all T1 self-reports plus the EDE-Q; T3 includes all T2 self-reports plus the treatment content questionnaire (all) and LEAP feasibility and acceptance questionnaire (intervention group only). At T3, the SEDI is also performed by phone.

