##### BASS Core Facility

The BASS Core Facility is a secure and encrypted tool for collecting questionnaire data online available through Karolinska Institute. Participants are directed to a secure registration procedure including double authorization with phone and e-mail, and consent to the study through Bank-ID. They also choose their own log-in details which are used subsequently. Each participant is assigned a patient ID used for all further pseudonymization. After study consent, BASS is used for all assessments, BASS manages the timing of later assessments; activation messages to participants and eventual reminders are sent automatically. BASS stores all item level survey data for each participant as soon as one entire instrument is completed; the entire assessment battery does not have to be completed for data to be saved. BASS also stores personal information obtained through the registration procedure (social security number, e-mail, phone number) and study consent, and several types of process data. The contact details are used to send automatic assessment activation messages and reminders. All project related data are stored within BASS for each participant at all timepoints as long as the project is active.

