### Statistical methods

#### Outcomes (methods for analyzing primary and secondary outcomes)

To evaluate the LEAP treatment effect (primary objective) the data will be analysed per protocol and based on intention to treat. The first analysis will include all controls (TAU) and participants that complete the program (LEAP+TAU) and answer the questionnaires. The T3 assessment point will be used for post treatment data unless the participants completed the program before T2. Each continuous outcome measure will be used as a response variable in a linear regression model with group allocation and baseline value as predictors. Logistic regression will be used for categorical outcomes. Additional covariates in the models will include gender, clinic, and time between T1 and first treatment session. Since the removal of drop out and noncompliant subjects in the per protocol analysis may lead to overestimation of the treatment effect, we will also perform the same analysis on the basic of intention to treat. Here all subjects who were randomized to LEAP and answered the questionnaires will be included in the treatment group, independently whether they participated in the LEAP sessions. Assessment points with at least CET and EDE-Q will be included in analyses in relation to the primary outcome. If data is missing on CET and/or EDE-Q, the timepoint will not be considered for analysis. There will be no item level missing data (technically prohibited in BASS). The percentage of patients withdrawing from the program despite the initial intention to participate will be considered as a feasibility marker. To compare proportions of dropout and loss to follow-up within the groups, conventional two-sample Z-tests will be used. To identify prognostic factors associated with a good response to LEAP (secondary objective), the treatment group will be subjected to additional analysis where the outcome of interest is used as response variable in linear or logistic regression model and potential prognostic factors (e.g., BMI, type of ED) are used as predictors. These analyses will include all participants with complete data for each specific model.

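### Requiring both CET and EDE-Q before an assessment counts discards observed primary-outcome data, and the intention-to-treat set is limited to questionnaire responders

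*Protocol article*

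**What the plan says.** All references are to the protocol article.

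- **Statistical methods, Outcomes.** Each continuous outcome gets its own linear regression on allocation and baseline value; categorical outcomes get logistic regression. Assessment points enter the primary-outcome analyses only if they hold at least CET and EDE-Q. The next sentence is not restricted to any outcome: "If data is missing on CET and/or EDE-Q, the timepoint will not be considered for analysis".
- **Same section, intention to treat.** "Here all subjects who were randomized to LEAP and answered the questionnaires will be included in the treatment group", whether or not they attended sessions.
- **Outcomes and Instruments/measures.** Remission of the eating disorder diagnosis is a primary outcome, measured as a binary result by SEDI at T3. BMI at T3, a secondary outcome, is taken in the same interview.
- **Self-report and interview data.** The questionnaires are completed online. "At T3, the SEDI is also performed by phone".
- **BASS Core Facility.** Each instrument is stored once it is finished: "the entire assessment battery does not have to be completed for data to be saved".
- **Blinding.** Participants know their arm; the clinicians who make the diagnostic assessments do not.

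**The concern.** No CET model needs EDE-Q, no EDE-Q model needs CET, and a remission model needs neither. The rule nevertheless lets a missing questionnaire decide whether a different, observed outcome is analysed. Because the data system stores instruments one by one and does not allow item-level gaps, missingness occurs by whole instrument, which is exactly the unit on which the rule acts.

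Two things are at stake. The first is precision, in a trial that already expects 30% drop-out. The second is selection: membership of the set called intention to treat depends on a post-randomisation event, namely returning self-report forms in an open-label trial. The article adds this analysis because the per-protocol one may overestimate the effect, so conditioning on response works against its own purpose. The outcome least exposed to participants' knowledge of their arm, the blinded remission interview, would be filtered through the forms most exposed to it.

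**Working it through.** **1. Reproduce the planned size.** The Sample size section opens with these inputs: "Based on pilot data and power analysis with beta = .80, alpha = .05, effect size f = .25". It adds a pre-post correlation r of .50 and arrives at 98 patients, 49 per arm. I read the .80 as power and use an F test at 5%, since sidedness is not stated. For a baseline-adjusted comparison of two equal arms, the noncentrality is

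λ = f²N / (1 − r²), with 1 and N − 3 degrees of freedom.

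At N = 98, λ = 0.0625 × 98 / 0.75 = 8.17 and power is 0.808. The smallest even N reaching 0.80 is 98, which matches. Enrolment of 128 matches 98 × 1.30 = 127.4, rounded up. The same formula is used in step 3.

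**2. SEDI results discarded.** The article gives no completion rate for the interview. Assume that its 30% drop-out means 30% lack at least one of CET and EDE-Q at the relevant assessment, so 128 × 0.70 = 89.6 have both. Assume also that everyone with both questionnaires is interviewed. If a proportion s has SEDI, the number discarded is 128 × (s − 0.70):

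| SEDI completed | Observed | Discarded |
|---|---|---|
| 70% | 89.6 | 0 |
| 80% | 102.4 | 12.8 |
| 90% | 115.2 | 25.6 |
| 100% | 128 | 38.4 |

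If some participants with both questionnaires are not interviewed, the loss at a given s is larger. It cannot exceed 128 × 0.30 = 38.4, because only those lacking a questionnaire can be dropped. SEDI is binary, so the power formula in step 1 does not apply to this table.

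**3. CET or EDE-Q scores discarded.** Assume each is completed by a proportion p. Without the rule, each model uses 128p. With it, each uses 128p² if missingness is independent and 128p if it coincides.

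| p | Rule, independent | Power | Rule, coincident (same as no rule) | Power |
|---|---|---|---|---|
| 80% | 81.9 | 0.73 | 102.4 | 0.82 |
| 90% | 103.7 | 0.83 | 115.2 | 0.87 |

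At 80% the rule thus costs each model between 0 and 102.4 − 81.9 = 20.5 participants. At 90% it costs between 0 and 115.2 − 103.7 = 11.5.

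**4. Does anything exempt SEDI?** The first sentence of the rule covers analyses of the primary outcome, and remission is one of the primary outcomes. The second sentence carries no restriction, so BMI at T3 may be caught as well. The later sentence about complete data for each model follows the prognostic-factor analysis in the LEAP arm and does not govern the comparison between arms. There is a further gap: participants who finish LEAP before T2 have T2 as their post-treatment point, but SEDI exists only at T3. The text does not say which assessment's questionnaires would decide whether their SEDI result counts.

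**The case against.** Several objections carry weight.

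- **SEDI is not named in the rule.** A reader might infer that the plan openly throws remission results away. It does not say so. Assessment timepoints are described as occasions for completing questionnaires, with the phone interview as an addition, so a rule confined to questionnaire outcomes is a plausible intention. What stands is that the literal wording includes SEDI and nothing excludes it.
- **Loss at T3 is not always fatal.** A reader might infer that anyone seen at T2 but lost at T3 contributes nothing. That is wrong for most of the LEAP arm: those who finish before T2 use T2 as the post-treatment point, and the article expects most to do so. It could apply to late finishers, and perhaps to controls, whose time point is less clear.
- **The loss may be small.** At T2 and T3, CET and EDE-Q sit in one online battery, with three automatic reminders and then personal contact. Missingness may largely coincide, so independence is the pessimistic case, and any single figure would be unsupported.
- **Allocation is preserved.** LEAP participants stay in their arm whether or not they attend, and loss to follow-up is compared by Z-tests. This is a recognisable available-case analysis. The comparison of losses describes a difference between arms but does not correct for one.
- **The rule gives one common set across outcomes.** That is a convenience, but separate regressions do not need it.

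**Conclusion.** The concern holds in limited form. The rule as written deletes observed CET scores when EDE-Q is missing and the reverse, and by its literal wording deletes observed SEDI remission results as well. The intention-to-treat group is a responder set. Both features reduce precision or make inclusion depend on returning open-label forms, and the analysis models require neither.

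The size cannot be derived from the article. Under the stated assumptions, the SEDI loss lies between 0 and about 38 of 128. With each questionnaire 80% complete, the analysable number is 82 to 102 and power about 0.73 to 0.82, at f = .25 and r = .5. If missingness coincides completely across instruments, the rule costs nothing; the documents do not show whether it will. The direction of any selection bias is unknown.

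**What to change.** 1. Delete the requirement for both CET and EDE-Q.
2. Analyse each outcome in every randomised participant with that outcome observed, in the assigned arm.
3. State that SEDI remission, and BMI at T3 from the same call, count whenever the interview was done, regardless of questionnaire completion.
4. Describe the responder-only set as an available-case set rather than as full intention to treat.

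A mixed model over T1 to T3 is optional. It would cut across the plan's post-treatment point, which depends on when LEAP was completed, and so is more than a wording change. A sensitivity analysis counting missing remission as not remitted is also optional, and is commonly left to the analysis plan.

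The cost is a few sentences and minor programming, with no new data. The downside is that the number analysed may differ slightly between outcomes, so each result should carry its own denominator.

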##### Secondary research questions

Are there initial factors (e.g., BMI, emotion regulation, compulsivity) that predict a more favorable outcome for patients in the LEAP group? Is LEAP perceived as a feasible and acceptable treatment for patients?

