#### Study design

The trial is a naturalistic two-armed parallel open-label superiority randomized efficacy trial, with recruitment from four Swedish specialist ED clinics. Eligible adult patients will be recruited via the clinics and randomized to treatment as usual (TAU) or TAU+LEAP, where LEAP will run in parallel with TAU. Key outcome variables in both arms are measured at initial assessment, after 3 months, and 6 months after initial assessment. Although most TAU+LEAP participants are expected complete the LEAP program prior to T2 assessment, a few may terminate LEAP prior to T3 (see Participant timeline).

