#### Data collection methods (Table 2)

##### Data from medical journals

The project uses ED diagnosis from SEDI or EDE, BMI, and the EDE-Q rating as part of T1 data. If project inclusion takes longer than 3 months after initial assessment, these measures are reassessed at the units.

**Table 2 Tab2:** Schedule of LEAP enrolment, interventions, and assessments (SPIRIT figure)

			STUDY PERIOD			
		Enrolment	Pre-assessment	Allocation	Post-allocation	Close-out
TIMEPOINT	***-t***_***1***_	0	***t***_***1***_		***t***_***2***_	***t***_***3***_

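### Predictors of response to LEAP are sought in the LEAP arm alone, which can show prognosis among LEAP recipients but not response to LEAP

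*Protocol article*

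**What the plan says.** The protocol article words the secondary question in two ways.

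- Under Secondary research questions, it asks whether there are initial factors that "predict a more favorable outcome for patients in the LEAP group". BMI, emotion regulation and compulsivity are given as examples.
- Under Statistical methods, Outcomes, the aim opens with "To identify prognostic factors associated with a good response to LEAP (secondary objective". The method follows at once: "the treatment group will be subjected to additional analysis where the outcome of interest is used as response variable", in a linear or logistic regression where "potential prognostic factors (e.g., BMI, type of ED) are used as predictors".

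No control patients and no group-by-factor term enter these models. The only further condition is that participants have complete data for the model in question.

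The sections on interventions and participant timeline state that both arms receive TAU, with LEAP added in one. On measurement, the Study design section says: "Key outcome variables in both arms are measured at initial assessment, after 3 months, and 6 months after initial assessment". At baseline, "T1 includes self-reports CET, DERS, DSM-5, and Active-Q", and from the records, "The project uses ED diagnosis from SEDI or EDE, BMI, and the EDE-Q rating as part of T1 data". Neither statement is limited to one arm. Among the instruments, the only one so limited is the "LEAP feasibility and acceptance questionnaire (intervention group only") at T3.

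**The concern.** A regression of outcome on a baseline factor among patients who all received TAU plus LEAP shows which patients end up better. It does not show whether they did better because LEAP helped them more. A patient with a higher BMI or fewer emotion-regulation difficulties may also do better under TAU alone. In that case the factor is prognostic and says nothing about LEAP.

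The statistical section fixes both the population (LEAP arm) and the model (no interaction) while wording the aim as response to LEAP. If the results are reported in those words, ordinary prognostic factors will be presented as predictors of benefit from the programme. The reverse error is also possible: a factor that truly modifies the LEAP effect can be missed if its prognostic effect runs the other way. The controls, who could separate the two, are to be measured on the same factors and outcomes.

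**Working it through.** **Inputs from the protocol article (Sample size).** 49 evaluable patients per arm, 98 in total; 64 enrolled per arm; 30% dropout; alpha 0.05. Two sizes for the LEAP arm follow: 49 as planned, and 64 x 0.70 = 44.8, about 45, after the stated dropout.

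**The plan's own figure.** There is none for the predictor analysis. The 98 for the main comparison does reproduce. It is the between-groups test of a repeated-measures ANOVA with 2 groups, 2 measurements, f = 0.25 and correlation 0.50. The noncentrality is 98 x 0.25² x 2 / (1 + 0.50) = 8.17, and the power is 0.808. So 49 per arm is a sound basis for what follows.

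**Assumptions.** The article gives no correlation between a baseline factor and outcome. The 0.50 in the Sample size section is between pre- and post-measures. I therefore assume factor-outcome correlations r of 0.2 to 0.5, the same in both arms.

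**Step 1: what the LEAP-arm slope estimates.** Write the outcome as Y = d·T + p·X + m·X·T + error, with T = 1 for LEAP, X the standardised factor, p its prognostic effect and m its modification of the LEAP effect.

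- Slope in the LEAP arm: p + m
- Slope in the control arm: p
- Difference, which is the arm x factor term: m

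The LEAP arm alone gives only the sum.

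**Step 2: a purely prognostic factor (m = 0), 45 LEAP patients, Fisher z.** The chance of a significant result is about Φ(atanh(r) x √(n − 3) − 1.96).

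- r = 0.3: 0.3095 x √42 = 2.01; Φ(0.05) = 0.52
- r = 0.4: 0.4236 x √42 = 2.75; Φ(0.785) = 0.78

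**Step 3: the same by simulation, compared with the interaction test.** 20,000 trials per setting, m = 0, share of trials with p < 0.05:

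| Assumed r | LEAP-only, 49 | Interaction, 49 per arm | LEAP-only, 64 | Interaction, 64 per arm |
|---|---|---|---|---|
| 0.2 | 29% | 5% | 36% | 5% |
| 0.3 | 56% | 5% | 68% | 5% |
| 0.4 | 83% | 5% | 91% | 5% |
| 0.5 | 97% | 5% | 99% | 5% |

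The LEAP-only rate rises with prognostic strength and sample size. The interaction test stays at its nominal level.

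**Step 4: the opposite error.** With p = −0.4 and m = +0.4 at 49 per arm, the LEAP-arm slope averages 0. It is flagged in 5% of trials, while the interaction test detects the modification in 55%.

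**Step 5: what the interaction test can detect.** With 80% power the detectable m is (1.96 + 0.84) x √(1 − r²) x √(2/(n − 3)).

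- 49 per arm: 2.80 x √(2/46) = 0.58 at r = 0, falling to 0.51 at r = 0.5
- 64 per arm: 0.51 at r = 0, falling to 0.44 at r = 0.5

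Units are SD of outcome per SD of factor.

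**The case against.** The strongest reply is that the protocol never claims to study moderation. The Secondary research questions section asks who does better within the LEAP group, and the statistical section itself calls the factors prognostic. For that question a one-arm regression is the right tool, and the percentages above for a purely prognostic factor are simply its power to find a true association. This stands. A reader might infer that the secondary research question goes unanswered, and the article does not support that: the planned model answers the question as first posed. What remains is the statistical section's own wording of the aim as response to LEAP, which the one-arm method cannot deliver.

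A reader might also infer that the controls are neglected more generally. They are not: the treatment-effect models include them, with group allocation as a predictor.

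A third reply is that interaction tests have little power at this size. That is true (step 5), and it limits what can be learned. It does not turn a LEAP-arm slope into evidence about treatment effect.

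Finally, the article does not say that predictor results will decide who is offered LEAP. Its Discussion regards the programme as suitable for nearly all patients with compulsive exercise. The harm is therefore one of misinterpretation, and an effect on patient selection is only a possibility.

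**Conclusion.** The concern holds in a limited form. The planned LEAP-only regression can describe prognosis among LEAP recipients, but it cannot support statements about response to LEAP. If it is read that way, a factor with no bearing on the LEAP effect would be reported as a predictor of response in about half of analyses at an assumed correlation of 0.3, and in roughly four fifths at 0.4, against 5% with an interaction test. These rates rest on assumed correlations, equal in both arms, with a continuous outcome and a single standardised factor. The argument in step 1 does not depend on those values.

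This is a stated choice of population and model, so it is not a detail left to an analysis plan. It concerns a secondary objective only.

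**What to change.** In the statistical section, fit the predictor models on both arms with terms for arm, factor and arm x factor. Report the interaction estimate with its confidence interval as the exploratory evidence on response to LEAP. LEAP-only associations may still be shown, described as prognosis among LEAP recipients. If the investigators want only the within-LEAP question, the minimum change is to reword the aim in the statistical section to match the Secondary research questions section and drop the reference to response.

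The cost is wording and a little analysis. No new measurement is needed, because the baseline factors and outcomes are already planned for both arms; according to Trial status, recruitment had not begun, so the change can be made before any data are seen. The downside is imprecision. At 49 per arm only interactions of about 0.5 to 0.6 SD of outcome per SD of factor are detectable with 80% power, and the report should say so, so that a non-significant interaction is not read as proof that LEAP works equally for all.

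### The LEAP-arm models for predictors of good response do not commit to adjusting for the outcome's baseline value, so factors that only track initial severity may be reported as predictors

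*Protocol article*

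**What the plan says.** The Statistical methods section of the protocol article (Outcomes) describes two regression analyses.

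- **Treatment effect (primary objective).** Each continuous outcome is the response in a "linear regression model with group allocation and baseline value as predictors". Gender, clinic and time from T1 to the first treatment session are added as covariates.
- **Factors behind a good response to LEAP (secondary objective).** The analysis is confined to the treatment group. The outcome of interest is the response in a linear or logistic model, and "potential prognostic factors (e.g., BMI, type of ED) are used as predictors". Participants with complete data for the given model are included. The outcome's baseline value is neither named nor ruled out, and good response is not defined as a change score or in any other way.

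The matching question under Secondary research questions is: "Are there initial factors (e.g., BMI, emotion regulation, compulsivity) that predict a more favorable outcome for patients in the LEAP group"? Both lists of factors are introduced as examples.

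The Sample size section gives "effect size f = .25 and an estimated correlation between pre- and post-measures of .50", and "a total of 98 patients are required: 49 patients receiving LEAP and 49 controls".

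**The concern.** The stated aim is to learn who responds well. With the end score as response and no baseline term, the model describes who ends at a low or high level. That depends partly on where each patient started.

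Emotion regulation and compulsivity can reasonably be expected to correlate with initial EDE-Q and CET scores, although the article gives no correlations. A factor of this kind, with no link to the course of illness beyond initial severity, inherits an association with the end score through the pre-post correlation.

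The sign can mislead as well. A severity marker goes with a worse end score but also with a larger drop, so patients who improved most could be labelled poor responders. Advice on whom to offer LEAP could then rest on initial severity alone.

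**Working it through.** **Inputs from the Sample size section.** Pre-post correlation 0.50; f = 0.25; alpha 0.05; power 0.80 (printed there as beta); 49 evaluable and 64 enrolled patients per arm; 30% drop-out. A third size, 64 × 0.70 = 44.8, or about 45, is what remains per arm if 30% of those enrolled are lost.

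**Assumed.** The correlation r between a factor and the baseline score is not given, so a range of 0.2 to 0.7 is shown. Tests are two-sided at 5%.

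**Step 1: the plan's own figure.** The article states no figure for the predictor models, so the check is on the total of 98. Take the between-groups F test of a two-group, two-measurement repeated-measures ANOVA, with λ = f²·N·m / (1 + (m − 1)ρ):

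- N = 98: λ = 0.0625 × 98 × 2 / 1.5 = 8.17; with 1 and 96 df, power is 0.808.
- N = 96: λ = 0.0625 × 96 × 2 / 1.5 = 8.00; power is 0.799.

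So 98 is the smallest even total that reaches 0.80, and it reproduces. This supports using 49 and 0.50 below.

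**Step 2: the mechanism.** Let B be the standardised baseline, Y = 0.5B + e the end score (variance of e = 0.75, so Y has variance 1), and X a factor with corr(X, B) = r and no effect on Y given B.

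- corr(X, Y) = 0.5r.
- Improvement is B − Y, with variance 1 + 1 − 2 × 0.5 = 1, so corr(X, B − Y) = r − 0.5r = 0.5r.

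The same factor is therefore equally strongly associated with a worse end score and with a larger improvement.

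**Step 3: how often X is declared a predictor.** Simulation, 20,000 runs per setting, one factor tested at a time:

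| LEAP patients | r = 0.2 | r = 0.3 | r = 0.5 | r = 0.7 | Baseline in model, any r |
|---|---|---|---|---|---|
| 45 | 10% | 16% | 38% | 67% | about 5% |
| 49 | 10% | 18% | 42% | 71% | about 5% |
| 64 | 12% | 22% | 51% | 82% | about 5% |

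Hand check by Fisher's z at n = 49, r = 0.5: atanh(0.25) × √46 = 0.2554 × 6.782 = 1.73, and P(Z > 1.96 − 1.73) is about 0.41, against 0.42 simulated. At r = 0.3: 0.1511 × 6.782 = 1.02, which gives about 0.18 with both tails.

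The rate rises with sample size, so better retention does not remove the problem.

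**Step 4: which outcomes are exposed.**

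- *Remission (SEDI at T3):* everyone enters with an eating disorder diagnosis, so there is no varying baseline value. Not affected.
- *BMI:* initial BMI is a named factor. Not affected when it is in the model.
- *EDE-Q scales and CET subscales (primary), DERS (secondary):* exposed unless the outcome's own initial score is among the factors in that model.

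**The case against.** The strongest reply is that the fault is read from silence. The list of factors is open, the outcome's initial score is an obvious prognostic factor, and a condensed article may leave the covariates of a secondary, within-arm analysis to an analysis plan that is not at hand. Some of the examples may themselves supply the missing term: emotion regulation would be initial DERS, and the listed instrument closest to compulsivity is the CET. This stands to a point. A reader might infer that the plan leaves baseline out, and the text does not say that. What remains is that the article chose to describe this model's population, response and predictors, named baseline for the neighbouring model, and made no such commitment here. An open list of candidate factors does not ensure that an adjustment needed in every such model is made.

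A second reply is that the secondary question asks about favourable outcome, and a severity marker does predict the end score in that sense. Unadjusted prognosis is a legitimate question. But the Statistical methods section speaks of good response to LEAP, and the end level alone does not measure that.

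Third, the size depends on assumed correlations. No figure in the article links BMI or type of eating disorder to initial CET or EDE-Q. The simulation also tests one factor at a time; other severity-related factors in the same model would reduce the effect. Both remarks stand, so the figures are a range and not a forecast.

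A reader might also ask for clinic in these models. No calculation here supports that, and the sentence on additional covariates could be read to cover them.

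**Conclusion.** The point holds as a gap in commitment, not as a stated error. If the predictor models are run without the outcome's baseline value, a pure severity marker may be reported as a predictor of good response on the EDE-Q, CET or DERS in about 10% to 42% of trials with 49 LEAP patients, against about 5% with baseline included. This rests on the plan's pre-post correlation of 0.50, an assumed factor-baseline correlation of 0.2 to 0.5, and a factor with no effect given baseline. The 71% at a correlation of 0.7 is the upper end of the range shown.

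Three stronger readings are not supported. Severity markers will not necessarily be reported; at a weak correlation the excess over 5% is modest. The problem does not extend to remission or BMI. And adjusting for baseline would not turn the analysis into one of response to LEAP: with no controls in the model, it cannot separate a factor that forecasts the course under any care from one that alters the benefit of LEAP. The adjusted result is prognosis within the LEAP arm.

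The treatment-effect analysis is untouched, since it already includes baseline. This is a free improvement to a secondary analysis.

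**What to change.** In the secondary-objective part of the Statistical methods section, state that every prognostic-factor model for a continuous outcome includes the T1 value of that same outcome as a covariate: the initial EDE-Q score for an EDE-Q scale, the T1 subscale score for a CET subscale, the T1 total for DERS. Add that results will be described as prognosis within the LEAP arm given initial severity, and not as differential response to LEAP.

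The cost is two sentences and one degree of freedom per model. The values are already collected and already used in the treatment-effect models, so no new data, visits or patients are needed.
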